## Abstract

**Background:**

The prevalence of obesity among children remains high. Given obesity’s significant lifelong consequences, there is great interest in preventing obesity early in life. There is a need to better understand the relation of common infant feeding styles and practices to obesity in infants using longitudinal study designs. There is also an urgent need to understand the role of caregivers other than mothers in feeding. A better understanding of variation in feeding styles and practices can inform the identification of risk groups and the tailoring of interventions to them.

**Methods:**

In partnership with Early Head Start programs across four counties in southern California, mothers and infants will be enrolled in a two-year longitudinal study collecting survey and anthropometric data. A subsample of mothers and their selected other caregivers will participate in qualitative research involving feeding diaries and dyadic interviews. The results will be used to develop and test an enhanced nutrition education program.

**Discussion:**

We outline a study methodology to examine feeding styles and practices and their association with early childhood obesity risk and enhance an existing intervention to promote healthy infant feeding and growth among children in low-income families.

## Background

Obesity prevalence among infants, toddlers, and preschool children in the United States (US) has doubled from the 1970s to the twenty-first century [1, 2]. Although rates have generally stabilized among some populations, racial/ethnic and socioeconomic disparities persist [3, 4]. For example, 9.4% of Latinx infants have a weight-for-length > 95th percentile relative to 6.6% of non-Latinx white infants. Although there has been a growing literature to better understand risk factors for obesity early in life, it remains unclear how feeding impacts early life risk for obesity among racial/ethnic minority children [5–9].

The American Academy of Pediatrics recommends exclusive breastfeeding as the optimal form of infant nutrition for the first 6 months and continued supplemental breastfeeding for 1 year. At 6 months, they recommend the introduction of a wide variety of nutrient-dense complementary foods. Starting at 9 months, they recommend three nutrient-dense meals and two or three small nutrient-dense snacks per day. Despite these guidelines racial/ethnic minority infants consume too many energy-dense foods and insufficient fruits and vegetables. Nationally representative research showed non-Latinx Black and Latinx infants between 6 and 11 months had lower intakes of fruits and vegetables and greater intakes of sweet and salty snacks compared to non-Latinx White infants [10, 11]. Research consistently shows common feeding practices deviate from these guidelines and are potential risk factors for early childhood obesity and targets for intervention: formula feeding, [12–16] combination feeding (breastmilk and formula), and the early introduction of solid foods [17, 18]. Other practices, such as early introduction of sugar sweetened beverages, are associated with obesity among older children and adults, [19] but their relation to obesity in infants is less explored [20, 21]. Research documents racial/ethnic disparities in these and related practices, such as feeding sugary drinks and “baby” cookies, [22] directing baby to empty the bottle, or propping the bottle [19, 23]. Such research offers insight into what infants are eating, but tells us little about how infants are fed.

Infant feeding styles and practices comprise the attitudes and behaviors that characterize caregivers’ approaches to maintaining or modifying children’s eating behaviors. We have limited information associating these feeding styles and practices with early childhood obesity [20, 21]. Responsive feeding, which involves properly interpreting and responding to the infant’s signals, is the recommended style [24]. Ethnic minority caregivers are more likely to exhibit non-responsive feeding styles (e.g., pressure feeding) relative to non-Latinx whites [6]. This difference in styles may be contributing to observed early-life obesity disparities [6]. Additionally, low levels of acculturation to the dominant American culture may be related to non-responsive styles and practices, [20, 25, 26] but results are inconsistent [27]. A better understanding of variation in feeding styles and practices can inform the identification of risk groups and the tailoring of interventions to them, as well as examining these relationships over time can help draw causal inferences and associations [28, 29].

Other caregivers (e.g., grandparents) are commonly involved in infant care and feeding, especially in ethnic minority families [30]. Non-parent caregivers’ infant feeding behaviors, especially those of relatives, have been associated with early childhood obesity [31–34]. However, there are only a handful of existing obesity interventions for young children that incorporate caregiver feeding styles and practices with nutrition advice, [35–37] and even fewer that account for the involvement of multiple caregivers in infant feeding [38]. They also start too late. Most begin with school-age children and target children 6 to 12 years of age [39]. The first 1000 days of life (i.e., conception through 24 months) constitute a critical period for optimal nutrition and development. Obesity interventions during this time period especially for low-income ethnic minority children, are still lacking [40–44]. Furthermore, few studies have engaged federally-funded programs, such as Early Head Start (EHS), which provides child development and family support services to infant and toddlers under the age of three in low-income families across the US [45].

To address these gaps, we developed the Grow Well/Crecer Bien project, a five-year community based participatory research (CBPR) study that is engaging EHS program leadership, staff, and families in the enhancement of existing nutrition education aimed to promote healthy infant feeding practices in the context of low-income families. The research aims to: 1) examine infant feeding styles and practices and their relation to infant growth and obesity in low-income families, 2) examine the role of other caregivers in infant feeding, and 3) develop and test an enhanced intervention, based on the information gained from the first two aims, that will address parents’ and other caregiver’s feeding styles and practices.

In this study we build on the Family Ecological Model to examine the social-ecological context that shapes infant feeding and child health, access to nutrition education, and the application of nutrition education to family systems [46]. This model provides structure when examining how factors in multiple systems operate together to shape child health. The microsystem includes the infant and their family. This unit is nested within the mesosystem that is the caregiving context (all the people who care for an infant). It may include a diversity of child caregiving knowledge and experience and a diversity of cultural values and norms shaping child care behavior. At the macrosystem level are public programs such as those serving low-income families. These programs influence the caregiving arrangements families make for their children and influence child health by shaping infants’ eating and, potentially, caregivers’ feeding. By viewing infant feeding in its ecological context, we can better understand how nutrition education translates to practice, affecting infant growth and obesity, and how the context could be better supported to improve child health. Furthermore, by incorporating multiple caregiver infant feeding into an intervention, we better address the diversity of U.S. families in terms of their caregiving context, reducing disparities using culturally appropriate programming.

The ultimate goal of this study is to reduce disparities in childhood obesity by incorporating healthy feeding styles and practices and multiple caregivers’ perspectives into existing nutrition education programs for low-income families. Our preliminary research with low-income Latina mothers in EHS identified the need for research to better understand and address the role of other caregivers. We showed that multiple caregivers, especially grandmothers, are involved in Latinx infant feeding. Although mothers understand the importance of healthy feeding, they may struggle to implement their knowledge in multiple-caregiver infant feeding contexts, increasing the risk for unhealthy infant growth and early childhood obesity [47]. This study addresses these latter concerns first by conducting a longitudinal study to characterize the caregiver context of infant feeding in low-income families and then by developing and testing a version of EHS nutrition programs enhanced by the incorporation of content addressing healthy feeding styles and practices with multiple caregivers.

## Methods

### Project overview

We use principles of CBPR, a collaborative approach combining the strengths of diverse partners and including all equitably in the research partnership [48]. In line with this approach, we will convene a community advisory board that meets quarterly, oversees the research, and approves all steps of the project. The research includes two phases. Figure 1 provides an overview of each phase of the research.

**Fig. 1 Fig1:**
[figure not shown]
Overview of the two study phases

Phase 1 is a mixed-method longitudinal study intended to characterize the caregiver context of infant feeding in low-income families. We hypothesize that non-responsive feeding styles and non-recommended feeding practices will predict steeper infant growth trajectories and obesity status. To test this hypothesis, we will create a cohort of 300 mother-infant pairs to assess variation in mothers’ feeding styles and practices and model the relation of feeding styles and practices to infant growth from 2 to 24 months and obesity at 24 months. We will also obtain feeding data and in-depth information from a subsample of 36 mothers and their identified other caregivers to provide contextual data on other caregivers’ involvement in infant feeding.

Phase 2 will utilize qualitative methods to develop content to be added to EHS’ existing nutrition program to create the enhanced intervention. Approximately 30 EHS-enrolled families and 30 EHS staff will participate in focus groups. This phase also involves a pilot cluster randomized controlled trial comparing the enhanced program to the existing program. Thirty EHS-enrolled mothers will participate in the trial.

Before we started the research, the University of California Riverside Institutional Review Board (IRB) approved all data collection procedures, study instruments, and informed consent documents. Additionally, the study team and EHS programs completed Memoranda of Understanding outlining roles and responsibilities in the partnership.

### Sites and partnerships

The study is being conducted in partnership with EHS programs. The federally funded EHS program helps low-income mothers of children aged 0 to 3 years support the healthy development of their children through home- or site-based education and support services. EHS provides nutrition education through classes, opportunities to meet with nutritionists, and referrals to community nutrition resources. The classes follow the My Healthy Plate guidelines aligned with the U.S. Department of Agriculture’s healthy eating practice campaign (www.choosemyplate.gov), the cornerstone of government-sponsored nutrition programs for low-income mothers and children (https://wicworks.fns.usda.gov/nutrition-education). The curricula encourage portion control, food diversity, and nutrition content. Classes also include information on parental roles and responsibilities for food preparation and family meal time.

The study involves partnerships with EHS programs across four bordering counties in southern California: Imperial, Orange, Riverside, and San Bernardino (see Fig. 2). These counties are characterized by often-overlapping pockets of high poverty and ethnic minority populations. Latinxs constitute the largest minority group in these counties -- 84.6% in Imperial, [49] 34.2% in Orange, [50] 49.6% in Riverside, [51] and 54% in San Bernardino [52] – with the largest subgroup, by far, being Mexicans. African Americans constitute the next largest minority group in Imperial (3.4%) [49], Riverside (7.2%) [51] and San Bernardino counties (9.4%) [52]; and the third largest minority group in Orange county (2.1%) [50]. While 12.8% of California’s population lives in poverty, [53] the poverty rates in three of these counties exceed the state average. A fifth (21.4%) of all persons live in poverty in Imperial [49], 12.7% in Riverside, [50] and 14.9% in San Bernardino [52]. Childhood obesity rates are likewise exceedingly high. Nationwide, 17% of children aged 2 to 19 years are obese [3]. Among California fifth graders, 49% of children in Imperial, 36% in Orange, 40% in Riverside, and 42% in San Bernardino counties are obese [54].

**Fig. 2 Fig2:**
[figure not shown]
Location of Early Head Start Partners

### Phase 1 - longitudinal study

During in-person visits when infants are 2, 6, and 12 months of age, trained study team members will administer^1^ individual face-to-face surveys with mothers (1.5 to 2 h) and collect anthropometric data from mother and child. During a 30-min visit at 24 months, anthropometric data only will be collected. Data will be collected as close to the infant’s target age as possible within a 3-month window, while facilitating maximal coordination with EHS programming and accommodation of families’ schedules. Visits will be part of regularly scheduled EHS visits and will take place either at the mother’s home or an EHS center. EHS staff will be present during data collection. Survey and anthropometric data will be recorded on laptops in Qualtrics, a web-based data collection software program. A subsample of 36 mothers from the cohort and 36 trusted other caregivers identified by these mothers will participate in feeding diary data collection when the infants are 2 and 6 months old and a dyadic interview when the infants are 6 months old.

#### Eligibility and recruitment

EHS staff, specifically home-based educators and center-based teachers, will facilitate the recruitment of mothers into the study. These staff members have direct contact with mothers either through weekly home-based visits or center-based daycare services. Prior to the start of recruitment, the study team held trainings with EHS staff in the four counties to provide an orientation to the study, including an overview of CBPR and the academic team’s partnership with EHS, the research aims, and recruitment procedures. During the training, home-based educators and center-based teachers along with EHS leadership decided on aspects of the recruitment procedures. Specifically, the discussion determined how to communicate among EHS staff/ supervisors and the study team when participants were identified.

To create a cohort of 300 mothers and their infants, EHS staff will distribute study flyers with eligibility criteria and study contact information to mothers on their caseload who are pregnant or who have an infant between the ages of 0 to 2 months. When mothers express interest, EHS staff will share the name and age of the child with the study team. Eligible mothers and their infants are enrolled in the study. Mothers must meet the following eligibility criteria: 1) be biologically female, 2) be 18 years of age or older, 3) have a child between ages 0 to 2 months that was born as a singleton, had a normal birth weight (greater than or equal to 5 lbs., 8 oz.), and be enrolled in EHS, 4) speak English or Spanish, and 5) be able to participate in four interviews over 2 years.

To recruit mothers and trusted other caregivers into the qualitative subsample, we will use purposive (non-random) sampling to identify mothers who reflect the sociocultural distribution of the quantitative cohort in terms of ethnicity and linguistic acculturation. We anticipate three groups within the subsample: English-speaking Latinas, Spanish-speaking Latinas, and mothers of other ethnicities. We expect that 12 mothers per group will achieve data saturation [55]. At the 2-month quantitative data collection visit, we will ask mothers if they consent to provide qualitative data in the form of: a) feeding diaries using the Baby Connect App when the infant is 2 and 6 months of age, the latter time point being associated with the introduction of solid foods, and b) a dyadic interview with the mother and trusted caregiver when the infant is 6 months. We will select 36 mothers on a rolling basis. Each mother must identify a trusted other caregiver to the focal infant to participate in a dyadic interview. Other caregiver inclusion criteria follows the Nurture Observational Study that examined multiple caregiver feeding effects on infant growth among a sample of minority (primarily African American) mother-child dyads [38]. A caregiver is any adult regularly involved in at least 3 h or more of infant care per week. This includes fathers, other partners, or non-parental caregivers (e.g., other family members, neighbors, babysitters, or childcare providers).

#### Survey measures

Infant weight and length will be measured to produce the two dependent variables: infant growth and obesity. Weight will be measured to the nearest 0.1 kg using calibrated Seca scales. Recumbent length will be measured to the nearest 0.5 cm using standard length rods. We will use the Centers for Disease Control (CDC) and Prevention SAS Macros for the World Health Organization (WHO) growth charts to convert weight and length measures into z-scores. WHO reference standards of gender-specific weight-for-length z-scores at ages 2, 6, 12, and 24 months will be used to evaluate infant growth and obesity.

Infant growth will be calculated as the growth trajectory over the first 24 months of life, using growth curve models of weight-for-length z-scores. We will explore the trajectory with different starting points, using the infant’s birth weight-for-length (reported by mother and converted to z-score) as baseline z-scores.

Obesity at 24 months will be calculated by the child’s body mass index (BMI), the standard clinical measure of obesity in children 2 years and older. We will assess this measure as kilograms of weight per square meter of length, and derive age- and gender-specific BMI percentiles, weight-for-age and BMI-for-age z-scores according to US national standards.

Feeding styles will be measured by the Infant Feeding Style Questionnaire (IFSQ), [56] which has 63 items on infant feeding beliefs and behaviors and 20 additional behavioral items related to solid feeding for children over 6 months of age. The questionnaire captures five feeding styles (i.e., laissez-faire, pressuring, restrictive, responsive, and indulgent) previously validated in a low-income sample of parents of infants and toddlers. Feeding practices will be measured by the 28 items (33 at 12 months) from the Baby Basic Needs Questionnaire (BBNQ) [57] pertaining to feeding, such as whether the child is breastfed exclusively or in combination with formula, when breastfeeding ended (if applicable), whether the child is exclusively formula fed, whether the child is fed solid foods, when solid foods were introduced, and what solid foods and other beverages are fed.

Covariates will be included in analyses as appropriate. At the 2-month visit, we will obtain infants’ birth weight and length, gestational age, and gender. We will also obtain mothers’ pre-pregnancy weight and height, gestational weight gain, age, level of education, race, ethnicity, acculturation (via the 42-item Abbreviated Multidimensional Acculturation Scale) [58], and levels of depression [59] and anxiety [60]. We will also obtain information about the household: zip code, highest level of education, total income, receipt of benefits, food insecurity, density (the number of people living in the home and the square footage of the residence), home ownership, childcare, and level of household chaos. At the 12-month visit, we will also measure mothers’ height and weight (see Additional file 1 for survey).

#### Statistical analysis

The study will use feeding styles and practices as two-way treatments, resulting in nested mixed models. In such models the fixed effects will be feeding styles (treated as a categorical variable with 5 levels for 5 feeding styles) and practices (treated as factors of composite scores for each feeding practice, such as exclusive breastfeeding and the introduction of solid food). The random effects will be caused by two types of correlations: those due to the infant characteristics, such as weight, and those due to clustering at multiple time points and within sites (infants’ families educated at the same sites). Accordingly, the R squared of the mixed model is expected to be at least 60%. The overall significance level α for a two-sided test is 0.05, and power 80%. Due to item similarities in a construct, the proposed significance level must be adjusted by the Bonferroni correction for multiple comparisons. In this study, the smallest adjusted significance level will be 0.0008 for each item in the construct of feeding beliefs and behaviors (0.05/63 items used in the construct of feeding practices). In addition, the hazard ratio across time points will be 1 for any reference level or group. Under these predefined conditions, the sample size will be 292, which was calculated in G*power 3.1.9.2.

Multiple imputation will be used if more than 5% of data is missing despite our efforts to prevent missing data. We will consider two types of effects: fixed and random. Thus, generalized linear mixed models will be ideal to analyze the data. Feeding styles and practices will be two categorical variables with fixed effects on the growth z score and obesity. Random effects will result from the nested grouping structure of infant families clustering in the same sites (like children in school classes) and the correlation between the variables, such as infant weight, collected from the same subjects across four time points. We will use generalized linear mixed models to examine if and how feeding styles and practices are associated with infant growth and obesity over time, and we will adjust these models for important covariates (e.g., mother’s pregnancy weight and age). Strongly associated items will be kept; all others will be excluded from further data analysis.

Generalized linear mixed models will be built to assess how the different constructs and/or sub-groups of feeding styles and practices relate to infant growth and obesity, adjusting for important covariates. We will employ Poisson regression to predict obesity, measured as the count of infants who became obese. The effect sizes for infant growth will be presented as how their weights change the score mean and/or summations of different constructs and their subgroups over time. The effect sizes for obesity will be presented as hazard ratios to evaluate comparative contributions of the construct and/or different sub-groups to obesity over time. Results of these analyses will be: 1) clustering of feeding style and practice items into subconstructs and subgroups which can be identified as meaningful clusters; 2) variation in feeding styles and practices within the sample; and 3) as whole latent variables, how these constructs or their subscales comparatively affect infant growth and obesity. This information will inform the development of the enhanced intervention components.

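### Feeding style is coded as one five-level category, although the questionnaire yields five scores per mother and the same section also models construct scores; the two must be reconciled

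*Protocol article*

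**What the plan says.** Under Survey measures, one instrument, the IFSQ, is used for style: "The questionnaire captures five feeding styles (i.e., laissez-faire, pressuring, restrictive, responsive, and indulgent"). It has "63 items on infant feeding beliefs and behaviors and 20 additional behavioral items related to solid feeding for children over 6 months of age". Practices come from the BBNQ: "Feeding practices will be measured by the 28 items (33 at 12 months) from the Baby Basic Needs Questionnaire (BBNQ").

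Under Statistical analysis (Phase 1), style enters the mixed model as "feeding styles (treated as a categorical variable with 5 levels for 5 feeding styles"). The next paragraph repeats the categorical coding: "Feeding styles and practices will be two categorical variables with fixed effects on the growth z score and obesity". Practices are also described there as composite scores, one for each practice.

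Further on in the same section, growth effects are to be expressed as "how their weights change the score mean and/or summations of different constructs and their subgroups over time", and the constructs or their subscales are also to be treated as latent variables. The qualitative analysis section likewise compares caregivers by IFSQ scores.

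Surveys take place at 2, 6 and 12 months. The 24-month visit collects anthropometry only.

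**The concern.** A five-level factor places each mother in exactly one style. A mother who scores high on both pressuring and indulgent, or close to equally on responsive and restrictive, has to lose one of them. The protocol gives no rule for doing this. A factor with 4 degrees of freedom and a set of five scores are different models with different estimands, and the text does not say which one tests the Phase 1 hypothesis that non-responsive styles predict steeper growth and obesity. With both open, the choice could be made after the results are seen, and Phase 1 findings feed the Phase 2 intervention.

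A second, conditional matter concerns scoring over time. The item sets grow with infant age. If a construct that gains items is summed, its score moves for a reason unrelated to behaviour, along the same time axis as the growth model.

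**Working it through.** **1. The plan's own figures.** The adjusted alpha reproduces: 0.05/63 = 0.00079, stated as 0.0008. The sample size of 292 cannot be reproduced because no effect size for feeding style is stated. The effect sizes below are therefore assumptions.

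**2. Inputs.** N = 292 is the stated size. N = 258 is 300 × 0.86, where 86% is the average retention in prior trials cited under Tracking and retention; it is not a planned figure. Assumed: five normal style scores with pairwise correlation 0 to 0.3; one style related to the outcome with standardised effect b = 0.20, 0.25 or 0.30; each mother assigned to her highest standardised score; one outcome per infant.

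**3. Information kept by the category.** The share of the relevant score's variance that lies between groups is the sum over groups of (group share) × (group mean of that score)². For five uncorrelated standard normal scores the expected maximum is 1.163. The score averages 1.163 in its own group (one fifth of mothers) and -1.163/4 in the other four.

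- Correlation 0: 0.2 × 1.163² + 0.8 × (1.163/4)² = 0.270 + 0.068 = 0.34.
- Correlation 0.3: 0.34 × (1 - 0.3) = 0.24.

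The category keeps about a third to a quarter of the score's variance.

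**4. Power on a like-for-like basis.** The fair comparator for the 4-df factor is the joint 5-df test of all five scores, both at alpha 0.05. For the joint test the noncentrality is λ = N × b²/(1 - b²), with an F test on 5 and N - 6 df:

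- N = 258, b = 0.20: λ = 258 × 0.04/0.96 = 10.75, power about 70%.
- N = 292, b = 0.30: λ = 292 × 0.09/0.91 = 28.9, power about 99%.

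Simulation with 3,000 replicates at N = 258 (ranges run over correlation 0 to 0.3):

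| Standardised effect | Five-level factor | Joint test of five scores |
|---|---|---|
| 0.20 | 20-28% | 70-71% |
| 0.25 | 31-42% | 90-91% |
| 0.30 | 43-61% | 98% |

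With N = 292 included, the full ranges are about 20-67% for the factor and 69-99% for the five scores. Taking the least and most favourable cases, the relative loss runs from 1 - 20/70 = 71% to 1 - 67/99 = 32%.

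**5. Sensitivity.** With N = 292 and other effect patterns (several styles relevant, or the responsive score shifted upwards), the category keeps 5-48% of the outcome variance that the five scores explain. At R² = 0.04 and alpha 0.05, power is 0.14-0.43 with the category and 0.75-0.77 with five scores. At alpha 0.0008 and R² = 0.0566 it is 0.01-0.14 against 0.48-0.51. The direction is the same in every setting tried. With standardised scores, 48-55% of mothers would have their top two styles within 0.5 SD, so the label would often turn on a small difference.

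**6. Scoring over time.** The IFSQ goes from 63 to 63 + 20 = 83 items over 6 months of age; the BBNQ goes from 28 to 33 at 12 months. The protocol does not say how many added items fall to each style or practice composite, so no shift per construct can be calculated. A sum rises with item count; a mean does not, although its content changes unless the items are common to all visits. Because visits may fall within a 3-month window, item sets might also differ between infants at the 6-month visit.

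**The case against.** Several points on the other side have force.

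- **A reader might infer that every mother is forced into one category and that nothing else is planned.** The text does not support that. The same section also plans means, sums, subscales and latent variables. What stands is that the categorical coding is stated twice, is contradicted later, and has no assignment rule.
- **A reader might infer that most of the power is lost.** The protocol gives no effect size, score correlation or assignment rule, so no such figure follows from it. At an effect of 0.30 with uncorrelated styles the loss is under half. The calculation also uses one outcome per infant rather than the planned repeated-measures mixed model. What stands is the direction and a substantial loss.
- **A reader might take 83/63 = 1.32 and 33/28 = 1.18 as the inflation of the scores.** Those ratios describe totals over a whole questionnaire. The plan proposes none: it speaks of "score mean and/or summations of different constructs and their subgroups over time", and of separate composites for each practice.
- **The choice between mean and sum may be left to an analysis plan.** That is fair, so the comparability point is conditional on sums being used. A shift in item count common to all infants at a visit could also be absorbed by visit terms, although changes in scale and content would remain.

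The categorical coding itself is not omitted detail. The article states it, so it can be judged as written.

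**Conclusion.** The point holds in a limited form. The Statistical analysis section codes feeding style as one five-level factor, which treats as mutually exclusive five styles that the questionnaire captures together, and the same section then models construct scores. The two descriptions conflict and need one answer before analysis.

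If the factor were built from the highest score, its power would be about 20-67%, against 69-99% for the five scores tested jointly. This rests on alpha 0.05, standardised effects of 0.20-0.30, style correlations of 0-0.3 and N = 258-292. The effects, the correlations, the assignment rule and the use of 258 are assumptions.

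The loss of comparability across visits arises only if sums are chosen and only for constructs that gain items; its size is unknown. This should be changed, but it does not invalidate the data collection.

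**What to change.** 1. State one primary exposure: the five IFSQ style scores entered together as continuous covariates, each the mean of the items asked at every visit.
2. Score the solid-feeding items separately, from the visits at which they are asked.
3. Use item means over common items for any multi-item BBNQ composite.
4. State which earlier exposure value (2, 6 or 12 months) is linked to the 24-month outcomes. No survey is done at 24 months, so a time-varying exposure has no value there.
5. Keep any dominant-style label as descriptive only, with its assignment rule written down.
6. Restate the basis of the sample size for this coding, including the effect size assumed.

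The cost is analysis wording plus a restated sample size calculation. The same data are used, with no added visits or burden on families.
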